Additional unablatable CRLM should be resectable	Immunotherapy ≤6 weeks prior to the procedure
Maximum number of CRLM 10	Chemotherapy ≤6 weeks prior to the procedure
Resection for resectable lesions considered possible obtaining negative resection margins (R0) and preserving adequate liver reserve	Pregnant or breast-feeding subjects. Women of childbearing potential must have a negative pregnancy test performed within 7 days of the start of treatment
Resectability and ablatability should be re-confirmed by intra-operative ultrasound (IOUS) and full surgical exploration	Compromised liver function (e.g. signs of portal hypertension, INR > 1,5 without use of anticoagulants, ascites)
Eastern Cooperative Oncology Group status (ECOG) 0–2	Uncontrolled infections (> grade 2 NCI-CTC version 3.0)
American Society of Anesthesiologists (ASA) grade 1–3	Severe allergy to contrast media not controlled with premedication
Life expectancy of at least 12 weeks	Any condition that is unstable or that could jeopardize the safety of the subject and their compliance in the study;
Adequate bone marrow, liver, and renal function as assessed by local usual laboratory tests. As usual, these results should be judged by the local investigator and should be conducted within 7 days prior to definite inclusion. Written informed consent	Substance abuse, medical, psychological or social conditions

The total duration of the study is around 13 years considering an inclusion time of 3 years and a minimum follow-up period of 10 years. All participants will provide written informed consent.The flow diagram of is shown in Fig. 1.

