#### Eligibility

Potential candidates will be registered and undergo routine pre-procedural work-up: baseline full blood examination, carcinoembryonic antigen (CEA), bone marrow, liver, and renal function -, anaesthetic review, ceCT of the chest and abdomen and either an upper abdominal ceMRI or a total body ^18^F-FDG PET-CT using upper abdominal ceMRI as problem solver. Patients with ≥1 resectable and ablatable CRLM (≤3 cm), no extrahepatic disease and a good performance status (WHO 0–2) are considered eligible. Supplementary resections for resectable lesions > 3 cm and thermal ablations for unresectable CRLM ≤3 cm are allowed with a maximum number of CRLM of 10 (Table 1).

Eligible patients will be stratified into low-, intermediate- and high disease burden after assessment by an expert panel (Fig. 1). The panel, consisting of at least two diagnostic radiologists, two interventional radiologists and two hepatobiliary and/or oncological surgeons, will appoint lesions that are resectable and ablatable as target lesions, resectable and unablatable lesions as unablatable lesions and ablatable but unresectable lesions as unresectable lesions. All unablatable lesions should be resectable and all unresectable lesions should be ≤3 cm and ablatable. Because definitions of resectability and ablatability can vary dramatically from one center to the other and from one specialist to the other, the panel has to agree with the treating physicians’ treatment plan. If the panel disagrees, the panel and the treating physicians must reach consensus before the patient can be enrolled.

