#### Inclusion

After having obtained written informed consent by the outpatient clinic doctor, patients will be formally included. The patient should be scheduled to undergo the procedure within a time-frame of maximum 6 weeks hereafter. Patients suitable for either laparoscopic resection or percutaneous ablation (Subgroup A, low disease burden; 1–3 target lesions) will be randomized prior to the procedure. All other patients will undergo open laparotomy with surgical inspection of the abdominal cavity and intra-operative ultrasound (IOUS).

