#### Exclusion (drop-outs)

Despite improvements in preoperative imaging technology, the intraoperative use of ultrasonography remains of crucial importance [32]. The detection rate of preoperatively unknown lesions is still high (up to 50%) with considerable consequences on treatment strategy [32]. Following surgical inspection and IOUS the inclusion criteria need to be reconfirmed prior to randomization. If (1) a radical procedure is no longer considered safe or feasible, if (2) > 10 CRLM are present, if (3) extrahepatic disease is detected, or if (4) no lesion can be appointed as target lesion, the patient cannot be included in the study and will be treated as non-study object. Additional CRLM suitable for both resection and ablation ≤3 cm will be appointed as new target lesions. Additional unresectable lesions ≤3 cm that are suitable for thermal ablation should be ablated if possible and vice versa additionally detected unablatable lesions should be resected. Lesions, preprocedurally appointed as target lesions, that prove unsuitable for one treatment modality based on IOUS lose their status and should be treated with the alternate modality (lesion shifts from target lesion to unablatable or unresectable lesion).

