#### Primary and secondary objectives

The main objective is to prove non-inferiority of thermal ablation compared to hepatic resection in patients with at least one resectable and ablatable CRLM (≤3 cm) and no extrahepatic disease. Primary endpoint is OS. Main secondary endpoints are overall disease-free survival (DFS), time-to-progression (TTP), time-to-local-progression (TTLP), primary and assisted technique efficacy (PTE, ATE), procedural morbidity and mortality, length of hospital stay, assessment of pain and quality of life (QoL), cost-effectiveness ratio (ICER) and quality-adjusted life years (QALY).

Pain analysis will be performed using visual analogue scale questionnaires (VAS) assessed prior to, directly after and every 3 months after local treatment; administered pain medication will be registered. Quality of life analysis will be performed using European Organisation for Research and Treatment of Cancer Quality of Life questionnaires (EORTC-QLQ-CR29, EORCT QLQ-C30, EQ-5D) prior to, and every 3 months after local treatment. Patients who complete the quality-of life questionnaires at baseline and at least once during treatment and follow-up will be included in the analysis. The largest decrease in quality of life with respect to baseline will be calculated. The Wilcoxon rank sum test will be used to detect statistical differences between the two treatment arms.

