#### Statistical methods

All clinicopathological and procedural variables will be described and analysed. Continuous variables will be summarized with standard statistics including, means, standard deviations, medians and ranges. Categorical variables will be summarized with frequencies. When appropriate, box plots and cross tables will be used for descriptive statistics of continuous and categorical variables, respectively. *P*-values below 0.05 will be considered significant. All calculations will be generated by statistical package for social sciences software (SPSS®). Calculation of the number of patients that will be needed to address our primary endpoint with a power of 80% and a 5% type I error rate is described in the sample size calculation section.

Univariate survival analysis will be performed using the Kaplan-Meier method. Differences in survival lengths will be analysed using the log rank test. To determine hazard ratios (HR) for multivariate analysis, Cox regression will be used. Significance of differences for continuous and categorical data will be analysed using the Mann-Whitney U test and Chi-square test respectively. When appropriate, box plots and cross tables will be used for descriptive statistics of continuous and categorical variables, respectively. OS will be estimated by the Kaplan-Meier method with corresponding two sided 95% Cl’s for survival proportions.

Primary and assisted technique efficacy rates (PTE, ATE) defined as the percentage of target lesions that have recurred after the initial local treatment and after additional local treatments regardless of the technique(s) used to treat the recurrence with a minimum follow-up period of 12 months after the last focal therapy;- Direct and indirect total cost of care for both treatment arms will be registered in the cost-effectiveness data collection matrix. Based on this matrix a cost–utility analysis, measured in terms of years of full health lived, using quality-adjusted life years will be prospectively calculated. Cost-effectiveness will be expressed as an ICER, the ratio of change in costs to the change in effects.

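### Technique efficacy is counted per lesion while patients are randomized, and the only categorical test named, a plain chi-square, ignores that several target lesions can come from one patient

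*Protocol article*

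**What the plan says.** All places are in the protocol article.

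- **Endpoint status.** Primary and secondary objectives lists "primary and assisted technique efficacy (PTE, ATE") among the main secondary endpoints.
- **Unit of the endpoint.** Statistical methods describes PTE and ATE as "defined as the percentage of target lesions that have recurred after the initial local treatment" and after additional local treatments, with at least 12 months of follow-up after the last focal therapy. The denominator is target lesions.
- **Unit of randomization.** Sample size calculation and statistical considerations randomizes 618 patients, 309 per arm. Under Randomization, a patient's arm sets the planned treatment for all of that patient's target lesions.
- **Lesions per patient.** Inclusion describes the low-burden subgroup as "low disease burden; 1–3 target lesions". Table 1 sets "Maximum number of CRLM 10", a cap on all metastases, target and non-target. Exclusion (drop-outs) lets the count grow during surgery: "Additional CRLM suitable for both resection and ablation ≤3 cm will be appointed as new target lesions".
- **Test.** Statistical methods states: "Significance of differences for continuous and categorical data will be analysed using the Mann-Whitney U test and Chi-square test respectively". P-values "below 0.05 will be considered significant". No other test for a binary outcome is named, and the article does not mention correlation between lesions of one patient.

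**The concern.** The endpoint is counted in lesions, but the randomized unit is the patient. Lesions in one patient share the tumour biology and the liver, and usually the operator, technique and follow-up imaging. Positive correlation of their recurrences is therefore plausible. Because all target lesions of a patient are allocated to the same arm, the comparison is entirely between patients, and the correlation inflates the variance of the difference in full. A chi-square test on pooled lesions does not see this.

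Local control is where ablation has been most contested. The Discussion says that ablation-site recurrence has held back its wider use. A lesion-level test with an understated error rate could declare a difference in local control, in either direction, more often than the stated 5%.

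**Working it through.** **The plan's own figures.** The article gives no sample size, power or expected rate for PTE or ATE, so there is no figure to reproduce on this point. Its one sample-size figure concerns overall survival and does reproduce: (1.645 + 0.842)² / (0.25 × (ln 1.3)²) = 359.3 events, and 359.3 / 0.6 = 598.8, so 599. It does not bear on lesion-level endpoints.

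**Inputs from the article.** 309 patients per arm; nominal significance level 0.05; 1 to 3 target lesions in the low-burden subgroup; at most 10 metastases of any kind per patient.

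**Assumptions, not in the article.**
- ICC of lesion recurrence within a patient: 0.05 to 0.3.
- Recurrence per lesion: 10%, used in the simulation only.
- Target lesions per patient, two distributions:
  - S (1 to 3 lesions): probabilities 0.5, 0.3, 0.2.
  - L (1 to 10 lesions, skewed): probabilities 0.45, 0.25, 0.12, 0.06, 0.04, 0.03, 0.02, 0.01, 0.01, 0.01.

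**Step 1: weighted cluster size, E[m²]/E[m].**
- S: E[m] = 1.7, E[m²] = 0.5 + 1.2 + 1.8 = 3.5, ratio 3.5/1.7 = 2.06.
- L: E[m] = 2.34, E[m²] = 9.0, ratio 9.0/2.34 = 3.85.

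**Step 2: design effect and true type I error.**

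DE = 1 + (E[m²]/E[m] − 1) × ICC

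True type I error = 2 × (1 − Φ(1.96/√DE))

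A correct interval is wider than the naive one by the factor √DE.

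**Step 3: simulation check.** Beta-binomial recurrences, no difference between arms, pooled lesion-level test, 4,000 trials per scenario (simulation standard error about 0.3 percentage points at 5%).

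| Distribution | ICC | DE | √DE | Type I error, formula | Type I error, simulated |
|---|---|---|---|---|---|
| S | 0.05 | 1.05 | 1.03 | 5.6% | 5.6% |
| S | 0.1 | 1.11 | 1.05 | 6.2% | 6.2% |
| S | 0.2 | 1.21 | 1.10 | 7.5% | 7.6% |
| S | 0.3 | 1.32 | 1.15 | 8.8% | 8.6% |
| L | 0.05 | 1.14 | 1.07 | 6.7% | 7.0% |
| L | 0.1 | 1.28 | 1.13 | 8.4% | 7.6% |
| L | 0.2 | 1.57 | 1.25 | 11.8% | 11.7% |
| L | 0.3 | 1.85 | 1.36 | 15.0% | 15.3% |

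**Step 4: null check.** At ICC 0 the simulated rejection rate is 5.3% (S) and 5.6% (L), nominal within simulation error. With one lesion per patient DE = 1 whatever the ICC. The excess therefore comes from clustering alone.

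**The case against.** The strongest objection is that the article never assigns the chi-square test to PTE or ATE. The sentence is a general rule for categorical data. The technique-efficacy text stands in a separate paragraph, is grammatically incomplete, and names no comparison. The article condenses a longer protocol, and the test for one secondary endpoint is often left to the analysis plan.

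Part of this stands: linking the test to these endpoints is an inference. But the point does not rest on silence. The article states one rule for categorical outcomes and, in the same section, defines a lesion-level percentage without making an exception. Anyone who follows the text as written arrives at a chi-square test on lesions.

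Four stronger readings are tempting, and the article does not support them:

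- **Ten target lesions per patient.** Under Eligibility, supplementary treatments "are allowed with a maximum number of CRLM of 10". That cap counts all metastases, including those that are not target lesions, and a lesion can lose target status at intra-operative ultrasound. Ten target lesions is only a theoretical limit.
- **Planned confidence intervals are too narrow.** Intervals are announced for survival proportions only, none for PTE or ATE. The √DE column applies only if a lesion-level interval is reported.
- **Time to local progression has the same fault.** Nothing says that it is analysed per lesion.
- **Weighting by lesion count is itself an error.** Patients with more lesions do count for more, but that follows from choosing a lesion-level rate. A patient-level bootstrap of the pooled percentage would leave it unchanged.

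It is also fair to say that the size rests wholly on assumed correlations and lesion counts. With few lesions and a low ICC the error rate is close to nominal.

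**Conclusion.** The point holds, for two secondary endpoints. The stated categorical test does not fit an outcome counted per lesion in a trial that randomizes patients. If recurrences within a patient are positively correlated, the lesion-level p-values for PTE and ATE are too small.

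Over an assumed ICC of 0.05 to 0.3, the nominal 5% test has a true type I error of about 5.6% to 8.6% with 1 to 3 target lesions per patient, and about 7% to 15% with the skewed 1 to 10 distribution. The direction depends on a positive correlation, which is plausible but not quantified in the article. The size depends on lesion counts that the article does not give.

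A reader might infer that the non-inferiority conclusion is at risk. It is not: overall survival is counted once per patient, and its analysis is untouched. This is a correction that should be made, not a critical flaw.

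**What to change.** Keep PTE and ATE as percentages of target lesions, and add one sentence to Statistical methods saying that the arms are compared with a method that treats the patient as the cluster. Either of these would serve:

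- logistic GEE with the patient as cluster and robust standard errors, which is available in SPSS, the package that the article names; or
- a bootstrap that resamples patients rather than lesions.

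If an interval is reported for either rate or for their difference, take it from the same method. Reserve the plain chi-square test for outcomes counted once per patient.

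No new data are needed, provided that lesion records carry the patient identifier. The cost is larger p-values for PTE and ATE and wider intervals where reported: by a factor of about 1.03 to 1.15 with 1 to 3 lesions per patient, and 1.07 to 1.36 with the skewed distribution, under the assumptions above.

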#### Thermal ablation

The safety, feasibility and preferred type of thermal ablation(s) is at the discretion of the interventional radiologist. Ablations are performed according to the CIRSE quality improvement guidelines with an intentional tumour free ablation margin of at least 1 cm [34].

Patients with limited disease burden (max. 3 lesions ≤3 cm) and no contra-indications for a percutaneous approach will be randomized prior to the procedure. Contra-indications for a percutaneous approach are proximity of critical structures. To avoid collateral damage to intestines a minimum distance to the stomach, small bowel and colon of 15 mm should be respected. Laparoscopic approach is allowed. Pneumo- and hydrodissections are allowed. Pringle-manoeuvres are not allowed.

Following percutaneous ablations, a ceCT or ceMRI should always be performed for ablated lesions > 2 cm and for lesions 0–2 cm with radiologically unclear margins after the ablation. Unequivocal local site residues or insufficient tumour-free margins should be re-ablated (completion ablation) within 4 weeks after the initial ablation. If re-ablated within 4 weeks, the residue/insufficient margins count as technically unsuccessful ablations, but not as a tumour recurring event when assessing the primary technique efficacy, local progression-free and disease-free survival. Patients with limited disease burden plus a contra-indication for both percutaneous ablation and for laparoscopic surgery and patients with intermediate or high disease burden will be randomized during open laparotomy.

The probes are connected to compatible and commercially available generators. Ablations will be performed according to the protocols provided by the manufacturers. If necessary, the needle electrodes will be repositioned for one or more overlapping ablations. The proximity of a large portal or systemic vein or hepatic artery is no contraindication for performing the thermal ablation.

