## Discussion

The recently published primary efficacy rates (complete ablation after the first procedure) of RFA and MWA for small CRLM have approached the reported resection plane recurrence rates for similar sized lesions [6]^,^ [14–17], [21]. Hence the issue of ablation site recurrences, that has previously prevented its widespread adoption, may be outdated. The relative ease to percutaneously re-ablate potential site recurrences, nowadays in the setting of a one-day admission under conscious sedation, has further downgraded its relevance.

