### Radiofrequency ablation

Since its introduction in the late 90’s, RFA is the most studied and widely adopted ablative technique. It has emerged as a promising approach in the treatment of patients with unresectable CRLM. RFA has acquired its role in the treatment of patients with unresectable CRLM as a safe, well tolerated, easily repeatable and less invasive procedure [44, 45].

One major drawback of RFA is the heat-sink effect in highly perfused organs, such as the liver where a large tumour located near large vessels (> 3 mm diameter) is not properly treated because heat is lost to the flowing blood. Another risk of RFA is heat injury to vital structures in or surrounding the ablated area. For this reason, treatment of lesions in the proximity of other organs, large vessels and major bile ducts has to be performed with caution, and is sometimes contra-indicated [46].

The 90-day mortality of thermal ablation alone is very low (< 1%) and the complication rate is also low (6–9%) [6]. Applied to unresectable CRLM, 5-year survival rates are approaching the results reported after surgical resection, especially for patients presenting with a limited number of small-size lesions. The reported 5-year OS is 25–55% [21–29]. The recently presented long-term results from the only available randomized controlled trial shows a survival plateau of 36% after 8-years in patients with unresectable CRLM [6]. It is important to realize that these percentages are derived from studies where thermal ablation was used to treat unresectable lesions. Ruers et al. found a PFS of 16.9 months (95%CI 11.7–22.1) in a group of patients who received chemotherapy plus RFA (HR 0.63 [95%CI 0.42–0.95]). Of those 56 patients treated with RFA, 9 developed a local site recurrence (LSR) (16,1%) [6].

Complications can be divided into three different groups: related to probe placement (bleeding 0,7%, infection, tumour seeding 0–0,3%), related to energy delivery (damage to bowel, gallbladder, bile ducts 4,2%, grounding pad burns, post-ablation syndrome, hepatic vascular damage, liver failure 2,1%) and related to the general procedure (deep venous thrombosis, pulmonary embolism, referred pain, fever, nausea, vomiting, kidney failure) [47].

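### Primary and assisted technique efficacy are defined as the percentage of target lesions that recurred, which is a failure rate, so the arm with more recurrences would show the higher efficacy

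*Protocol article*

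**What the plan says.** The section on primary and secondary objectives lists, among the main secondary endpoints, "primary and assisted technique efficacy (PTE, ATE), procedural morbidity and mortality". The abstract lists them too.

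The only definition is in Statistical methods. The two rates are "defined as the percentage of target lesions that have recurred after the initial local treatment", and the assisted version continues "after additional local treatments regardless of the technique(s) used to treat the recurrence with a minimum follow-up period of 12 months", counted from the last focal therapy. The definition contains no 'not' or 'without'.

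Two other places bear on the term:

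- The Discussion speaks of "primary efficacy rates (complete ablation after the first procedure", which is a success rate.
- The Thermal ablation section says that residue or insufficient margins re-ablated within four weeks count as technically unsuccessful ablations, "but not as a tumour recurring event when assessing the primary technique efficacy, local progression-free and disease-free survival". This settles which events count. It does not say whether the rate is one of success or of failure.

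**The concern.** A rate called efficacy should rise when treatment works. This one rises when treatment fails. An analyst has two options: follow the text and report efficacy upside down, or depart from the text and choose the direction after the fact. Neither is satisfactory for a named main secondary endpoint.

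The endpoint matters to the trial's argument. The Discussion treats recurrence at the ablation site as the issue that has held back wider use of ablation, and PTE and ATE are the per-lesion measures of it. A reader who compares the arms on efficacy as defined would draw the reverse conclusion about local control.

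**Working it through.** The article states no expected value for PTE or ATE, so there is no figure to reproduce. The check is one of direction.

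**Inputs**

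- Definition: recurred target lesions divided by all target lesions (Statistical methods).
- Meaning of primary efficacy elsewhere: complete ablation at the first procedure (Discussion).
- Recurrence figure for illustration: 9 of 56 patients (Radiofrequency ablation section). It is per patient and comes from a cited trial in unresectable disease, whereas PTE is per target lesion.
- All other rates below are assumed.

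**Formulas**

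- Literal rate = recurred / total.
- Rate in the success sense = 1 − recurred / total.

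**1. Size of the mislabelling.** Literal: 9/56 = 16.1%. Success sense: 1 − 9/56 = 83.9%.

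**2. Ranking of the arms.** Assume 10% recurrence in one arm and 20% in the other.

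| | Better arm | Worse arm |
|---|---|---|
| Literal | 10% | 20% |
| Success sense | 90% | 80% |

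The literal rule gives the worse arm the higher efficacy.

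**3. Primary against assisted.** Assume 100 target lesions, of which 15 recur and 10 of those are then controlled by re-treatment.

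| | PTE | ATE |
|---|---|---|
| Literal | 15/100 = 15% | 5/100 = 5% |
| Success sense | 85/100 = 85% | 95/100 = 95% |

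Under the literal rule, successful assistance lowers assisted efficacy.

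**4. What does not change.** Recurred and not recurred are exact complements. The Chi-square test named for categorical data uses the same two-by-two table either way, so its p-value is the same. The absolute difference in step 2 is 10 percentage points both ways, with the sign reversed.

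The sample size uses only overall survival inputs: one-sided alpha 0.05, power 0.80, hazard ratio 1.3, event probability 0.6.

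- Events: (1.645 + 0.842)² / (0.25 × (ln 1.3)²) = 359.3.
- Patients: 359.3 / 0.6 = 598.8, i.e. 599 as stated.
- Inflated: 599 / 0.97 gives 618, and 618 / 0.90 gives 687, both as stated.

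None of these depends on PTE or ATE.

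**The case against.** The strongest reply is that this is a slip of one word that no competent analyst would follow. Assisted efficacy falling below primary efficacy is absurd enough to reveal the error, and the test result is the same in either direction. Most of that stands: a dropped 'not' is the likely cause, and no inference about a treatment difference is lost. It does not make the definition correct. The sentence is in the operative methods, nothing else in the article overrides it, and although an article may leave detail to a fuller document, that does not excuse a rule it states wrongly.

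A second reply is that the Discussion describes published rates and does not define this trial's endpoint. That is fair. Its sentence is also loosely built, since it sets efficacy rates beside recurrence rates at the resection plane. But its bracketed explanation plainly means success. The ordinary meaning of efficacy and the PTE-to-ATE ordering in step 3 point the same way.

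A reader might go further and infer that the four-week rule in the Thermal ablation section conflicts with the definition of primary efficacy, or favours the ablation arm because it is written for ablation only. The documents do not support this:

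- The rule is explicit and prespecified, and it fits an endpoint built on recurrence.
- The early failure is still recorded as a technically unsuccessful ablation.
- The supposed conflict arises only if the Discussion's bracketed phrase is treated as the trial's definition.
- The article gives no rate of completion ablation from which an advantage could be sized.

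**Conclusion.** The point holds as an error of direction and labelling in the definition of two main secondary endpoints. As written, PTE and ATE are failure rates, the arm with more recurrences scores higher, and ATE drops when re-treatment succeeds. In the article's own illustrative figure, the gap between what would be reported and what is meant is 16.1% against 83.9%. The 10% v 20% and 100-lesion examples are assumptions and serve only to show direction.

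A reader might infer that the between-arm analysis of these endpoints, or the trial's main conclusion, is compromised. It is not: the Chi-square p-value and the size of the absolute difference are the same for a rate and its complement, and neither the overall survival analysis nor the sample size uses these endpoints. The correction is worth making because it is cheap and because the endpoint cannot sensibly be reported as it is written.

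**What to change.** In Statistical methods, reverse the numerator:

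- **PTE:** the percentage of target lesions that have not recurred after the initial local treatment.
- **ATE:** the percentage of target lesions that have not recurred after additional local treatments, whatever technique was used for the recurrence.

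Keep the minimum of 12 months' follow-up after the last focal therapy. Leave the four-week counting rule as stated. It applies equally to PTE, local progression-free survival and disease-free survival, so changing it for PTE alone would split one rule across three endpoints.

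Alternatively, keep the numerator and rename both endpoints as primary and assisted recurrence rates wherever they appear: the abstract, the objectives, the Thermal ablation section, Statistical methods and the abbreviation list.

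The first option costs the rewording of two definitions. Neither option changes data collection, the test or the sample size. The chosen direction should be recorded before the endpoint is analysed.
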